#### Participant numbers

Sample size calculations are based on the analysis of the primary outcome, that is, the difference between placebo and CBD groups in total number of Cannabis-free Days over the 12-week intervention period. Ferguson has suggested that the minimum effect size (Cohen’s *d*) for an effect of practical clinical significance is 0.4167 [55]. To achieve 90% power (two-tailed) and α = 0.05, a total of *N* = 250 (*n* = 125 per group) participants are needed to detect a between-group effect size of *d* = 0.41. Of the target 250 sample, it is estimated approximately 20% (*n* = 50) of the study sample (*N* = 250) will be Indigenous Australians.

Participants who discontinue study procedures after commencing study interventions (medication dispensed on Day 1) will not be replaced in the study but will be included in the modified intention-to-treat analyses. Participants enrolled and randomised, but do not commence any treatment (no medication dispensed or other clinical interventions) will not be included in the final analysis.

#### Recruitment, screening and assessment

Participants will be recruited from people seeking treatment at participating study sites, and/or people interested in the study in response to study advertisements at local health services, social media, and clinical trial recruitment platforms. On initial contact with the service, potential participants will be informed of the study and if interested, referred to a site coordinator to complete telephone screening. Following telephone screening, potentially eligible participants will be scheduled a face-to face assessment with a Study Medical Officer (SMO) to confirm eligibility. Potential participants will sign a medical screen consent form prior to the SMO completing a structured history, clinical examination, and any laboratory investigations with the participants. The SMO will also explain the study requirements to the potential participant and explain the study medication and any potential side effects. Eligible participants are scheduled an appointment (Week 1, Day 1) to attend for enrolment into the study. For those participants who are not eligible or choose not to participate in the study, alternative treatment options will be organised in collaboration with the patient, as clinically appropriate.

#### Informed consent, randomisation and blinding

Written informed consent is obtained on Week 1, Day 1 of the study prior to the commencement of all subsequent study procedures. Consent is obtained with the site coordinator independent of treating clinicians, to minimise ‘pressure’ to participate in the study.

The randomisation schedule has been developed by an independent statistician, with eligible participants randomised in a 1:1 ratio between groups using variable block randomisation to help maintain blinding, with subjects stratified by (a) site (to achieve approximately equal numbers of active and placebo at each site) and (b) Indigenous Australian status (to allow direct between-group statistical comparisons within Indigenous Australian participants).

Participants, clinicians, and researchers involved in service delivery, data collection and analysis will remain blinded to study conditions using matched placebos manufactured by the same manufacturer. CBD and placebo will be packaged in identically labelled containers with the participant’s ID number and site. Aside from site trial pharmacists (who have no direct contact with participants), all other members of the clinical or research teams will be blinded to group allocation.

Unblinding will occur after all data are collected, entered, cleaned and the trial database has been locked. In circumstances where allocation needs to be unblinded (e.g. severe adverse event), the principal investigator will authorise the local site investigator to break the blind (via the site trial pharmacist).

### Interventions

#### Medications

The experimental condition will receive 12 weeks of CBD oral 400 mg daily, administered as 200 mg liquid administered twice a day (BD). The CBD used in the trial is a plant-extracted pharmaceutical product (registered in Australia as Epidyolex® for the treatment of paediatric epilepsy), and is an oral liquid (clear, colourless to yellow solution) containing 100 mg per ml, dispensed in 105 ml bottles. The placebo is identical in composition and appearance (with the exception of the CBD). Both CBD and placebo are manufactured and supplied by Jazz Pharmaceuticals.

The dose is selected based on the findings of the Phase IIa RCT [29] that identified a daily dose of 400 mg CBD being more efficacious than placebo at reducing cannabis use during 4-week treatment and follow up.

Nicotine dependent participants will be offered smoking cessation counselling during the trial, with prescriptions and supply of nicotine replacement therapy (NRT) either in the form of 16-h topical patches (7, 14 or 21 mg) and/or nicotine chewing gum or lozenges provided.

#### Counselling

All participants will receive four structured 40–50-min counselling sessions over the 12-week medication phase, based on cognitive behavioural therapy (CBT) and motivation enhancement for relapse prevention, consistent with identified ‘best practice’ for cannabis cessation interventions [56]. Available evidence suggests 4-sessions of CBT deliver comparable outcomes to 6 or more sessions for treating CUD [57]. Counselling will be delivered by psychologists experienced in CUD treatment and trained to deliver manualised counselling interventions. Study Counsellors will keep a log of attendance at counselling sessions.

#### Clinical reviews

Participants will have 3-weekly medical reviews with the SMO over the 12-week intervention (Weeks 1, 4, 7, 10 and Week 13). At each appointment, the SMO will review cannabis and other substance use since the last appointment, other health and social issues, and client goals, complete Concomitant Medications and Adverse Events assessments, collect UDS, and supply medications dispensed by the trial pharmacist.

### Outcome measures

The *primary outcomes* are illicit cannabis use during the 12-week intervention period, operationalised using two endpoints:*Cannabis-free Days* over the 12-week intervention period, producing a continuous measure between days 1 and 85. Details regarding number of days of cannabis use will be collected at each research interview (baseline week 1, weeks 4, 7, 10, week 13 and 25) using the Time Line Follow Back (TLFB) approach, a reliable and validated measure of cannabis use, particularly when combined with biological assays (e.g. UDS) and confidentially reported to independent researchers^74^.*Urinary quantitative analysis of THC-COOH (creatinine adjusted)*. Urine samples will be collected at weeks 1, 4, 7, 10, 13 and 25, and analysed using liquid chromatography-tandem mass spectrometry (LCMS). As THC-COOH can remain ‘positive’ using qualitative thresholds (e.g. 20 ng/ml in LCMS assays) for more than 30 days after abstinence in chronic heavy cannabis users [58], we will analyse quantitative levels of THC-COOH (creatinine adjusted) to detect differences in cannabis use between the two study groups, replicating the approach used in the pilot RCT [29] (see below).

Secondary outcomes (Table 1) include a range of measures that relate to cannabis use (including rates of abstinence or reduced frequency of cannabis use, cannabis withdrawal and cravings, cannabis related problems, severity of CUD), safety (adverse events), health outcomes (including mental health, physical health, QoL), consumer experience of the medication, cognitive performance, other substance use and post-treatment outcomes (12 weeks after the intervention). The relationship between experiences of racial discrimination (using the modified Everyday Discrimination Scale) and outcomes for Indigenous Australians will also be explored.

**Table 1 Tab1:** Table of all primary and secondary outcome measures included in study

Domain	Name	Description of measure	Administration timepoint
**Basic**	Demographics	7 Questions: basic demographics including: age, gender, sexuality, Aboriginal and Torres Strait Islander background, education level, employment status, relationship status and living situation. Categorical data, excluding age which is discrete numeric	Research Interview: Week 1 (baseline) Day 1
**Cannabis Use**	Modified Time Line Follow Back (TLFB) [64]	Cannabis free days, self-reported using a modified timeline follow back (TLFB). Week 1 and 25 interviews will ask about cannabis use in the preceding 4-weeks; week 4, 7, 10 and 13 interviews will ask about the preceding 3-weeks. Bounded count; number of days abstinence (out of 84)	Research Interview: Week 1 (baseline), 4, 7, 10, 13 and 25
	Diagnostic & Statistical Manual of Mental Disorders (DSM-V) [65]	Severity of Cannabis Use Disorder in the prior 12-weeks using the modified (DSM-5 criteria) MINI scale. Number of DSM-5 CUD criteria met out of 11 (Mild CUD: 2–3; Moderate CUD: 4–5; Severe CUD: 6 +) Bounded count, number of DSM-5 CUD criteria met (out of 11)	Research Interview/ Clinical review: Week 1 (baseline), 13 and 25
	Cannabis Use History	7 semi-structured questions exploring: history and frequency of cannabis use and any previous attempts at reducing cannabis use. Continuous	Research Interview/ Clinical review: Week 1 (baseline)
	The Substance Use Goals Questionnaire (SUG)	Bespoke scale developed by addiction medicine specialists involved in the CBD-CUD Study. Participants goal towards their cannabis use. Measured using a self-reported substance use goals questionnaire: 2 items with 5 response categories. 5-level ordinal	Research Interview: Week 1 (baseline), 4, 7, 10, 13 and 25
	Rates of Abstinence	The proportion of participants who achieve pre-identified levels of abstinence from cannabis use (weekly rates), and a 50% reduction in cannabis use days compared to the pre-treatment 4-week period. Binary categorical (non-abstinent vs abstinent)	Research Interview: Week 1 (baseline), 4, 7, 10, 13 and 25
	Cannabis Withdrawal Scale (CWS) [51]	19 items on a 10-point Likert Scale, with 0 = Not at all to 10 = Extremely. The CWS is used as a diagnostic instrument to assess severity of cannabis withdrawal symptoms. Self-report over the last 24 h in 8 domains; irritability, depression, anxiety, cannabis cravings, physical symptoms, sleep difficulty, restlessness and appetite. Continuous (average item score as a 0–10 range, converted to a z-score)	Research Interview: Week 1 (baseline), 4, 7, 10, 13 and 25
	Marijuana Craving Questionnaire – short form (MCQ) [66]	12 items on a 7-point Likert scale, with 1 = strongly disagree to 7 = strongly agree. The MCQ is a self-report instrument that assesses marijuana craving along 4 dimensions; compulsivity, emotionality, expectancy and purposefulness. Continuous (average item score as a 0–10 range, converted to a z-score)	Research Interview: Week 1 (baseline), 4, 7, 10, 13 and 25
	Marijuana Problems Scale (MPS) [67, 68]	19-item MPS measuring potential negative effects of marijuana on social relationships, self-esteem, motivation and productivity, work and finances, physical health, memory impairment and legal problems on a 3-point Likert scale, with 0 = no problem, 1 = minor problem or 2 = serious problem. Continuous (total count of problems (0–19) or as a summed total of severity rating (0–38)	Research Interview: Week 1 (baseline), 13 and 25
	Urine Drug Screen	Urinary Drug Screen (UDS) collected to analyse for quantitative creatinine adjusted THC-COOH and CBD-COOH. Continuous (ng/ MoL)	Research Interview: Week 1 (baseline), 4, 7, 10, 13 and 25
**Other Substance Use**	Australian Treatment Outcomes Profile (ATOP) [69]	3-Part Questionnaire: 1. Substance use; items refer to substance use over the last 4-weeks, in particular: alcohol, amphetamines, benzodiazepines, heroin, other opioids, cocaine, other substances and tobacco 2. Injecting risk behaviour; 2-items exploring injecting behaviour in the last 4-weeks 3. Health and Well-being; 11-items investigating the participants’ accommodation arrangements, psychological and physical health and quality of life Bounded count (days of use/ abstinence in previous 28-days)	Research Interview: Week 1 (baseline), 4, 7, 10, 13 and 25
	Fagerstom Test for Nicotine Dependence (FTND) [70]	6-item questionnaire that measures nicotine dependency, with a total available score of 10. Continuous (range 0–10, converted to z-score)	Research Interview: Week 1 (baseline), 4, 7, 10, 13 and 25
**Mental and Physical Health**	Psychotomimetic States Inventory (PSIa) [71]	48-item questionnaire with subscales in delusional thinking, perceptual distortions cognitive disorganisation, anhedonia, mania, and paranoia. Continuous (range 0–48, total and subscale scores each converted to z-scores)	Research Interview: Week 1 (baseline), 7, 13, and 25
	PCL-5 for Post Traumatic Stress Disorder (PTSD) [72]	20-item self-report measure of the 20 DSM-5 symptoms of PTSD. The four domains consist of: Re-experiencing, Avoidance, Negative alteration in cognition and mood and Hyper-arousal. Continuous (range 0–80)	Research Interview: Week 1 (baseline), 13 and 25
	Patient Reported Outcomes Measurement Information System (PROMIS-29) v2.1 [58]	29-item self-report measure assessing the past 7-days. The seven domains include: physical function, anxiety, depression, fatigue, sleep disturbance, ability to participate in social roles and activities, pain interference and intensity. A 5-point Likert scale (range 1–5) to measure symptom severity or frequency. Continuous (total and subscale scores converted to a z-scores)	Research Interview: Week 1 (baseline), 4, 7, 10, 13 and 25
**Social/ Other**	Treatment Satisfaction Questionnaire for Medication (TSQM) [73]	14-item questionnaire across four domains focusing on drug effectiveness, side effects, convenience and global satisfaction of the medication. Continuous (range 0–100)	Research Interview: Week 4, 7, 10, 13 and 25
	Drug Effects Questionnaire-5 (DEQ-5) [74]	5-item questionnaire assessing consumer ratings of drug effects. Continuous (range 0–7)	Research Interview: Week 4, 7, 10, 13 and 25
	Testing the Blind	2-questions exploring the participants’ subjective opinion of study drug allocation. Binary categorical (placebo vs CBD) and continuous (% confidence)	Research Interview: Week 1 (baseline), 4, 7, 10, 13 and 25
	Safety Adverse Events	Adverse events assessed with study clinician to assess for any side effects of study drug. Unbounded count	Research Interview: Week 1 (baseline), 4, 7, 10 and 13
	Treatment Retention	Calculated from treatment records and participant withdrawal/ completion form. Discrete numeric (week of dropout)	Clinical review: week 13
	Modified Everyday Discrimination Scale (m-EDS) [75]	10-item instruments based on the Discrimination/ Racism in Everyday Life and 6-item instrument based on Discrimination/ Racism in Healthcare adapted to a diverse Aboriginal and Torres Strait Islander context. Participants are asked to report the extent to which they experience discrimination in different settings, with the response options of ‘not at all’, ‘a little bit, ‘a fair bit’ and ‘a lot’. Continuous	Research Interview: Week 1 (baseline)
	Qualitative research interviews	Qualitative research interviews will be conducted with Indigenous Australian participants who consent to participate. Qualitative methods will collect data on how participants’ experience of racial discrimination, identification with culture and community, and how their social and cultural networks (peers, family and local community) impact on attempts to change their cannabis use, as well as how participants perceive their cannabis use and identify their treatment goals and how participants engage with the study treatment procedures (medication, counselling and the role of Aboriginal Health Workers at study sites	1 interview during weeks 7–13 (flexible)
**Cognitive Assessment**	National Adult Reading Test 17-word version (NART17) [76]	The NART is a prevalent tool used in clinical scenarios to predict an individual’s prior level of intelligence, often crucial in neuropsychological studies and practices. The NART-17 consists of 17 written words in British English which all have irregular spellings. Continuous (scales converted to a z-score)	Research Interview: Week 1 (baseline)
	Rey Auditory Verbal Learning Task (RAVLT) [77]	Test of verbal learning and memory. Retention of a 15-item word list presented on 5 occasions. Number of words recalled on each presentation, following presentation of a novel list of 15 words; and then after brief and long delays recorded. Recognition of target stimuli also assessed. Continuous (scales converted to a z-score)	Research Interview: Week 1 (baseline) and 13
	Eriksen Arrow Flankers (with no-go) [78]	Speed of response to target stimuli flanked with either neutral, congruent or incongruent stimuli (24 each). Random 10% (n = 8) trials require with-holding of response (no-go). Reaction time: errors and false alarms recorded. Continuous (scales converted to a z-score)	Research Interview: Week 1 (baseline) and 13
	N-Back [79]	N-back is a continuous performance task to measure verbal working memory and is dependent on the integration of the frontal and temporal regions, two areas particularly affected by THC. Participants are instructed to monitor a series of stimuli and to respond whenever a stimulus is presented that is the same as the one presented *n* trials previously. Continuous (scales converted to a z-score)	Research Interview: Week 1 (baseline) and 13
	Digit Span Task [80]	Task evaluates working memory. The test consists of two-parts: (1) ‘Digits Forward’, requires the participant to repeat sequences of number in the order given; (2) ‘Digits Backward’, requires participant to recite the numbers in reverse order. Continuous (scales converted to a z-score)	Research Interview: Week 1 (baseline) and 13
	Trail Making Test (TMT) [81]	The TMT is a tool used to gauge an individual’s attention, processing speed and cognitive flexibility. It has two parts, in which the participant is instructed to connect a set of 25 dots as quickly as possible while maintaining accuracy. Continuous (scales converted to a z-score)	Research Interview: Week 1 (baseline) and 13

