#### Research interviews

The schedule of trial procedures and assessments for participants, including the timing of research and clinical interventions is shown in Table 2. Participants are scheduled to have interviews with researchers at 3-weekly intervals during the 12-week intervention (Weeks 1, 4, 7, 10 and 13), and again 12 weeks after the intervention (Week 25). These interviews will be face-to-face with a researcher, although they can be undertaken by telehealth if required. All data collected at researcher interviews will be entered directly into an electronic database, REDCap, and kept confidential from treating clinicians. Participants will be reimbursed with shopping vouchers for time, inconvenience, and expenses of attending research interviews [59].

**Table 2 Tab2:** Schedule of trial procedures and assessments

Assessment/ Procedure	Screening	Intervention Phase					Follow-up
**Week**	**-t**_**1**_	**1**	**4**	**7**	**10**	**13**	**25**

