#### Primary outcomes

We will model the effects of CBD on number of cannabis free days (out of 84 days) via single-level Gaussian regression with the outcome regressed on the main covariate experimental group (placebo vs CBD). Number of cannabis-free days in the 28 days prior to baseline will be included as a covariate to control for variation in participants’ prior frequency of use entering the study. Two treatment factors that could plausibly influence the primary outcomes and which vary across participants will also be included as covariates: number of counselling sessions attended during the study period (count variable range 0–4), and whether or not NRT was taken (binary variable measured at baseline: did not undertake NRT vs undertook NRT). If residuals are distributed normally, we will report the results from this analysis. If residuals are not distributed normally, we will treat cannabis-free days/84 as a bounded count instead of a numeric variable and use aggregated binomial regression with a logit link.

We will model urinary THC-COOH levels (a continuous outcome, in ng/MoL) via random-slopes mixed-effects models with the group, time (6-level categorical ordered predictor; Weeks 1 (baseline), 4, 7, 10, 13), the group × time interaction, number of counselling sessions attended, and whether or not NRT was undertaken as the fixed factors, and participant ID as the random factor.

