#### Secondary outcomes

All repeated measures of secondary outcomes will be modelled using the same approach as for urinary THC-COOH. That is, random slopes mixed-effects models for repeated measures regressions with group, time, the group × time interaction, number of counselling sessions attended, and whether or not NRT was taken as the fixed factors. These models will all be based on the generalised linear model, with link functions differing depending on the form of the outcome, as follows:Numeric (e.g., PROMIS-29 scores, marijuana craving questionnaire scores): Gaussian regression with identity link functionOrdinal (e.g., motivation to change cannabis use): ordinal logistic regression with logit link functionBounded count (e.g., severity of CUD) or binary (e.g., participant rating of group allocation): binomial logistic regression with logit link functionUnbounded count (e.g., adverse event count): negative binomial regression with log link function

See Table 1 for the form of each outcome measure.

Several secondary outcomes are single observations per individual. Group, number of counselling sessions attended, and whether or not NRT was taken will be the sole predictors in these models. Total abstinence from cannabis during weeks 10–13 (non-abstinent vs abstinent) and 50% increase in cannabis-free days during weeks 10–13 relative to cannabis-free days prior to baseline (< 50% reduction vs ≥ 50% reduction) will be modelled with binary logistic regression with logit link function, relative risk of adverse events during the trial period with negative binomial regression with log link function, hazard of treatment dropout via discrete-time hazard model with complementary log–log link function.

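### The on-treatment TLFB looks back a set three weeks rather than to the last interview, so a missed or off-schedule interview leaves avoidable gaps in the 84-day primary outcome

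*Protocol article*

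**What the plan says.** Table 1 (Outcome measures) sets two look-back lengths for the modified Time Line Follow Back. At baseline and follow-up, "Week 1 and 25 interviews will ask about cannabis use in the preceding 4-weeks". During treatment, "week 4, 7, 10 and 13 interviews will ask about the preceding 3-weeks. Bounded count; number of days abstinence (out of 84" days).

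The Primary outcomes paragraph of Data analysis models "number of cannabis free days (out of 84 days) via single-level Gaussian regression", with an aggregated binomial model over 84 as the fallback. The Research interviews section places the interviews three weeks apart, at weeks 1, 4, 7, 10 and 13, and says of the face-to-face format "although they can be undertaken by telehealth if required". Data analysis plans hierarchical multiple imputation for missing data.

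Two other places bear on the point. Under Clinical reviews, "the SMO will review cannabis and other substance use since the last appointment"; that is the medical officer's review, which is not named as the source of the endpoint. Under Secondary outcomes, "Total abstinence from cannabis during weeks 10–13 (non-abstinent vs abstinent") is an outcome in its own right, alongside a 50% change in cannabis-free days over the same weeks.

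**The concern.** A look-back of set length, counted from the interview date, reproduces the treatment period only when every interview is on its nominal day. Otherwise the days asked about and the days the endpoint is meant to cover are no longer the same.

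There are two distinct effects. A missed interview leaves a three-week hole that the next interview, read literally, does not fill. An early or late interview shifts the window: some treatment days are never asked about and others are replaced. The second effect is the less visible one. The four answers still add up to 84 days, so nothing appears missing and imputation is not triggered.

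At stake is observed data on a primary endpoint that could have been collected at almost no cost, and the correct placement of days in the weeks 10–13 outcomes, which rest on the week 13 interview alone.

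**Working it through.** **Inputs.** Look-back of 21 days at weeks 4, 7, 10 and 13, and a denominator of 84 (Table 1; Primary outcomes). Enrolment is on Week 1, Day 1, so three-weekly interviews fall on days 1 + 21k = 22, 43, 64 and 85. Treatment days are taken as 1–84. An interview on day v covers days v − 21 to v − 1.

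**The plan's own figure.** On schedule the windows are 1–21, 22–42, 43–63 and 64–84: 4 × 21 = 84, no gaps and no overlaps. The stated 84 reproduces.

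**Off schedule.** The size of each deviation below is an assumption chosen for illustration.

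| Deviation | Days never asked | Counted twice | Outside 1–84 | Total asked |
|---|---|---|---|---|
| Week 4 five days late | 1–5 (5) | 22–26 (5) | 0 | 84 |
| Week 7 seven days late | 22–28 (7) | 43–49 (7) | 0 | 84 |
| Week 4 three days early | 19–21 (3) | 0 | 3 before Day 1 | 84 |
| Week 13 seven days late | 64–70 (7) | 0 | 85–91 (7) | 84 |
| Week 7 missed, week 10 attended | 22–42 (21) | 0 | 0 | 63 |
| Week 13 missed | 64–84 (21) | 0 | 0 | 63 |

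One missed interview therefore leaves 21/84 = 25% of the outcome unobserved. A week 13 interview seven days late replaces 7 of the 21 days (one third) in the weeks 10–13 outcomes. Its effect on the 84-day count is only the difference in use between the lost and the substituted days, so at most 7 days either way.

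**How often, under assumed rates.** The article gives none. If each of the three interim interviews (weeks 4, 7 and 10) is missed independently with probability p, the proportion of participants with at least one hole is 1 − (1 − p)³:
- p = 5%: 1 − 0.857 = 14%
- p = 10%: 1 − 0.729 = 27%
- p = 20%: 1 − 0.512 = 49%

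Not all of these holes are avoidable, since some participants attend no later interview.

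If each of the four interviews is 0–5 whole days late, uniformly and independently around the named weeks:
- Days outside 1–84 equal the lateness of week 13: mean 2.5.
- The mean absolute difference between two such latenesses is (6² − 1)/(3 × 6) = 1.944, so the mean positive part is 0.972. Over three adjacent pairs, days counted twice average 3 × 0.972 = 2.9.
- Days never asked are the lateness of week 4 plus the same three gaps: 2.5 + 2.9 = 5.4 of 84.

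**Asking since the last completed interview instead.** An early or late week 4, 7 or 10 interview, or a missed one followed by an attended interview, gives 84 of 84 days covered once each. A week 13 interview seven days late gives 91 days, 7 of them after day 84, so dating and a cut at day 84 are also needed. A missed week 13 still leaves 21 days uncovered. The week 25 interview cannot recover them, because it looks back only four weeks.

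**The case against.** The strongest reply is that Table 1 is a summary. On schedule, three weeks back and back to the last interview are the same interval, and the article does not say what an interviewer does when a visit is late or missed. Visit windows and interviewer instructions normally sit in the full protocol, and their absence from an article is no fault. The endpoint itself is defined over the 12-week treatment period, so counting a day after day 84, or one day twice, would breach that definition. Nothing says that dates are discarded, and the weekly abstinence rates listed in Table 1 suggest that finer data than a 21-day total are held. Telehealth, reimbursement and three-weekly dispensing all favour timely contact. A uniform 21-day recall also has merit: a longer recall for poor attenders makes recall length depend on attendance.

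Much of this stands. It removes any claim that double counting or post-treatment days will occur, because dated answers could be realigned. It does not remove the gap: the article does state a look-back length, and days that were never asked about cannot be restored by realignment. A visit window would not cure this either, since any permitted deviation breaks the tiling while the look-back stays at 21 days. The different wording for the medical officer's review is not a contradiction, as that review has another purpose and assessor.

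**Conclusion.** The point holds as a cheap improvement of moderate importance. Followed as written, the stated look-back leaves 25% of a participant's primary outcome unasked after one missed interim interview, although the participant may attend the next. It also misaligns days around any early or late interview, including in the weeks 10–13 outcomes.

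A reader might infer more, and the document does not support it:
- Not every deviation corrupts the outcome. A missed visit creates only a gap, which the plan would impute; duplicated or out-of-range days come from early or late visits and can be removed if dates are kept.
- Biased treatment comparisons are not shown. Late or missed visits could be related to use or to arm, but the article gives no rates and no pattern, so neither the size nor the direction of bias can be derived.
- Lateness accumulating from visit to visit should not be assumed, because the schedule names fixed study weeks.

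The 25% follows from the stated figures. The 14%, 27% and 49%, and the averages of 5.4, 2.9 and 2.5 days, rest wholly on assumed attendance.

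**What to change.** At weeks 4, 7, 10 and 13, have the interviewer ask about every day since the last completed TLFB date (or Day 1) and enter answers by calendar date. Sum only study days 1–84 for the primary endpoint and only days 64–84 for the weeks 10–13 outcomes. After a missed interview, the next one covers the whole gap.

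The cost is one line in the interview instructions and a date field in REDCap. On-schedule participants notice no difference. The downside is a recall of 42 days or more after a missed visit; flagging those records would allow a sensitivity analysis. A missed week 13 interview and dropout are not recovered and still need the planned imputation. If the full protocol or site materials already work this way, amend Table 1 to match.
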